## Abstract

Until now, non-specific chronic neck pain has mainly been considered as a musculoskeletal system dysfunction, with associated psychological involvement due to its prolonged or recurrent nature. However, patients with non-specific chronic neck pain frequently additionally exhibit respiratory dysfunction. Emerging evidence suggests that addressing the respiratory dysfunction in these patients will provide additional therapeutic benefits in musculoskeletal and respiratory-related outcomes for several reasons (biomechanical, biochemical, and psychological). Motor control dysfunction of the muscles surrounding the spine (diaphragm included) negatively affects the mechanics and biochemistry of breathing (pH-homeostasis). An impaired and ineffective breathing pattern has been recognized as the primary source of many unexplained symptoms (anxiety, depression, confusion, chest pain, hypocapnia, and breathlessness) in patients with non-specific chronic neck pain. The proposed protocol’s purpose is dual: to assess the relative effectiveness of manual therapy in the cervical spine and the diaphragm, in combination with breathing reeducation exercises, along with cervical spine manual therapy or usual physical therapy care on the underlying dysfunctions in patients with non-specific chronic neck pain via a randomized controlled clinical trial, and to validate part of the outcome measures. Several musculoskeletal and respiratory dysfunction outcomes will be employed to delimit the initial extent and level of dysfunction and its resolution with the treatments under study.

## 1. Introduction

Chronic neck pain is one of the most commonly reported musculoskeletal pathologies in the general population [1]. It has an immense impact on the physical, social, and psychological aspects and quality of life of the individual and society as a whole [1]. A total of 223 million people are affected worldwide, and 22 million live for years with neck pain-related disability, according to the Global Burden of Diseases, Injuries, and Risk Factors Study 2019 [2]. The primary pathology and pathophysiology of chronic neck pain are still unclear and significantly contribute to morbidity and disability in everyday life and at work in many countries [1,3]. 

Mechanical neck pain is defined as pain and discomfort localized between the superior nuchal line, cervical spine, and the spinous process of the first thoracic vertebra. The pain may refer to another region, such as the scapula, anterior chest wall, head, or upper limb [4]. Chronic neck pain describes neck pain persisting for longer than 12 weeks or after the healing period, or recurring neck pain that intermittently affects an individual over a long period of time [5]. The anatomical sources of the pain appear to be several (facet joints, intervertebral discs, and myofascial tissues). Since, on most occasions, clinicians cannot identify the exact source of the pain, the pain is characterized as non-specific, and the diagnosis is based mainly on patients’ clinical signs and symptoms [6]. Clinicians must differentiate chronic neck pain related to serious pathologies (e.g., rheumatoid arthritis, metastatic bone disease) from biomechanical-related neck disorders [6]. 

People with non-specific chronic neck pain (NSCNP) present with local hyperalgesia, impaired conditioned pain modulation, low quality of life, and psychological disruptions (fear of movement, depressive symptoms, pain catastrophizing) [7]. Furthermore, cervical muscles not only stabilize the cervical spine, but contribute to respiration (sternocleidomastoid, anterior scalene, trapezius). These muscles frequently display diminished strength, endurance, motor control, and proprioception as a result of pain [7,8]. Neck pain may result in altered neck muscle activation levels and variable neck muscle activation sequences (incoordination patterns), including reduced participation of the deep segmental neck muscles and increased participation of the superficial neck muscles [3,8]. The above-mentioned pain-related dysfunctions contribute to forward head posture (FHP) maintenance, reduced active range of motion, and a poor and altered breathing patterns [9]. In consequence, the chemistry (pH blood levels) and respiration pattern may change, causing smooth respiratory muscle constriction, altered electrolyte balance, decreased tissue oxygenation [10], increased excitability in the nervous and muscular system, hypertonia of the accessory muscles, hypomobility of the thoracic cage, shortening of the accessory muscles, and a vicious circle contributing to the pain experienced in NSCNP [9,10]. Dysfunctional breathing (DB) presents in the form of changes in the blood chemistry, dysfunction of respiratory muscles, and a decrease in respiratory muscle strength and associated respiratory outcomes, such as maximum expiratory pressure (MEP), maximum inspiratory pressure (MIP), end tidal CO_2_ (ETCO_2_), forced expiratory volume in the 1st second of expiration (FEV1), maximum voluntary ventilation (MVV), and forced vital capacity (FVC) [8,9,10]. The three aspects of dysfunction contributing to NSCNP are presented in Figure 1.

Due to the complexity of chronic neck pain, mainly due to the diversity of factors associated with the development or persistence of neck pain, the treatment resources used in the rehabilitation of NSCNP vary, and there is conflicting evidence about the most appropriate therapeutic modalities [6]. Although patients with NSCNP have conventionally been treated by traditional physical therapy, manual therapy (spinal mobilization, manipulation techniques), education, or exercise [11], some do not experience complete recovery, suggesting the need for additional clinical approaches [10]. Based on the evidence underlying the observed respiratory dysfunction in patients with NSCNP [9], a previous cohort study incorporating breathing retraining management has demonstrated improved musculoskeletal and respiratory outcomes with significant functional improvement [10]. Jafari et al. [12] reported that hypoalgesia was more evident when breathing at a lower frequency with a low inspiration/expiration ratio; however, they did not definitively present the underlying mechanisms. Diaphragmatic breathing endogenously stimulates the vagus nerve. The latter response effectively suppresses peripheral inflammatory cytokine release, decreases sympathetic tone, activates the parasympathetic nervous system’s relaxation response, and contributes to pain control [13]. We contend that the addition of breathing reeducation exercises will decrease the respiratory rate, as well as restore dysfunctional breathing and the respiratory chemistry (end tidal CO_2_ increase, pH normalization, and improved tissue oxygenation), contributing to a decrease in the excitability of the nervous and muscular system, resulting in analgesia [10]. Additionally, breathing reeducation exercises would release the dome of the diaphragm, resulting in improvement in its descent, increased rib cage mobility, and muscle tone reduction in the accessory inspiratory muscles (anterior scalene, sternocleidomastoid, upper trapezius) and the external oblique [10]. Finally, the head’s posture and the cervical spine’s mobility will improve [8].

According to the International Federation of Orthopedic Manipulative Physical Therapists (IFOMPT), manual therapy (MT) is defined as: “a specialized area of physical therapy for the management of neuro-musculoskeletal conditions, based on clinical reasoning, using highly specific treatment approaches, including manual techniques and therapeutic exercises,” considering in parallel to the psychosocial state of each patient [13]. To improve musculoskeletal and respiratory outcomes, MT stimulates a number of biomechanical, neurophysiological, and psychologically mediated mechanisms [13]. The effectiveness of MT in musculoskeletal outcomes has been examined in numerous systematic reviews [11,14,15,16]. A previous systematic review presented evidence for the effectiveness of diaphragmatic MT (DMT) in increasing rib cage, spinal, and posterior muscle chain mobility in healthy adults, as well as those with a variety of musculoskeletal and respiratory conditions [17]. 

Only one previous systematic review, which mainly addressed the association between MT, respiratory parameters, and NSCNP, could be identified in the literature [18]. However, our subsequent systematic review demonstrated the lack of existing clinical trials in examining the effectiveness of mobilization techniques of the cervical spine and diaphragm in combination with breathing reeducation exercises for NSCNP relief [19]. Moreover, it highlighted the absence of clinical trials in analyzing the effectiveness of diaphragmatic manual techniques or cervical mobilization techniques as a single intervention regaridng respiratory outcomes in patients with NSCNP [19].

**Figure 1 diagnostics-12-02690-f001:**
[figure not shown]
The three aspects of chronic neck pain dysfunction, with corresponding references. (red arrow mean increase or decrease).

### Objectives of the Proposed Study

Based on these findings and the hypotheses underlying the observed respiratory and psychological dysfunction in patients with NSCNP, the aims of this study will be to assess: (1) the effectiveness of manual therapy in the cervical spine (CMT) and diaphragm (DMT), in combination with breathing reeducation exercises (BREx), on musculoskeletal and respiratory outcomes in patients with NSCNP, and (2) the effectiveness of CMT alone or conventional physiotherapy (CP) on respiratory outcomes. Additionally, two additional objectives relating to the initial development of the outcome measures used in this study will be to examine: (3) the construct and concurrent validity of specific respiratory outcomes relating to DB in patients with NSCNP, and (4) the reliability of biomechanical-based assessments.

## 2. Materials and Methods

### 2.1. Study Design

This protocol describes a randomized clinical trial (RCT) with a blinded assessor and participants, as well as the development/evaluation of several outcome measures in patients with NSCNP. We followed the SPIRIT (Standard Protocol Items: Recommendations for Interventional Trials) Statement to present this protocol [20]. The flowchart of the RCT is presented in Figure 2.

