### 2.9. Outcomes

The evaluations will take place at all time-points: before the treatment sessions (week 0), after ten treatment sessions (week 4), and four months after the beginning of the trial (week 16). The primary outcomes will be: functional disability (NDI) [25] and pain (VAS) [26]. Several secondary outcomes will also be evaluated: cervical range of motion (CROM) [27], craniovertebral angle (CVA) [28], Nijmegen Questionnaire (NQ) [29,30], Hi-Lo test [31], breath holding time (BHT) [32,33], single breath count (SBC) [34], end tidal CO_2_ (ETCO_2_) [35] and respiratory rate (RR) [36], chest wall expansion (CWE) [37], the Hospital and Anxiety Depression Scale (HADS) [38], the Tampa Scale for Kinesiophobia (TSK) [39] and adverse events [40]. All outcomes are briefly presented below. The corresponding references for each of the above outcomes include reliability and validity details, except for some further testing proposed in Section 2.10 and Section 2.11.

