#### 2.9.1. Primary Outcome Measures

The Neck Disability Index (NDI) [25]: The NDI is a disability self-report tool in relation to neck pain. It consists of 10 questions, with 6 alternative responses each, that relate to the ease of performing different tasks, pain severity, and the coexistence of headache. Each item’s score ranges from 0 (no pain and no functional limitation) to 5 (worst pain and maximum limitation), for a total score that ranges from 0 (no disability) to 50 (totally disabled).

Pain Intensity-Visual Analog Scale (VAS) [26]: Subjective pain intensity registration, by the selection of a value between 0 (no pain) and 100 (maximal pain) that best describes the intensity of pain felt in the last 24 h.

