### 2.12. Interventions

Ten treatment sessions will be administered to all participants, thrice for the first two weeks and twice for the third and fourth weeks, lasting for 40 min per session. The sessions will be individually administered in a reserved room with adequate lighting, music, and air conditioning. 

The manual therapy program will be applied by a physical therapist (main researcher), a clinical instructor of manual therapy, PhD candidate, with an OMT diploma from a recognized IFOMPT program, certified as Mulligan Practitioner, with two Master of Science degrees from the Athens Medical School, Greece, and 20 years of experience in clinical practice. A physical therapist with a Master of Science degree from the Athens Medical School and 17 years of experience in clinical practice will administer the traditional physiotherapy program (Group C) and the sham diaphragmatic manual therapy component (Group B). Sham diaphragmatic manual therapy will be administered via a therapeutic ultrasound device [43]. 

The participants can only receive the assigned treatment. They will be advised against combining the treatment they were allocated to with medication or other physical therapy approaches. Any deviation from the treatment sessions administration (missing more than one appointment) or any worsening of symptoms will be reasons for exclusion. The interventions proposed for each group are described briefly below, and in detail in the Supplementary Materials. All selected interventions are widely applied in the field of physical therapy and are safe when administered by appropriately trained physical therapists. 

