**Group A:** This group will receive CMT [44,45,46,47], DMT [48,49,50], and BREx [51,52]. Initially, cervical manual therapy (CMT) will be applied for 20 min, consisting of cervical spine inter-vertebral mobilization techniques, according to the Mulligan Concept, and soft tissue techniques. Subsequently, in order to indirectly stretch and mobilize the fibers of the diaphragm, diaphragmatic manual therapy will be used, which should result in improved muscle contraction and reduced tension. The doming diaphragmatic technique and the manual diaphragmatic release technique, both as described by Leon Chaitow, will be among the experimental techniques employed. For 10 min, both maneuvers will be performed in 2 sets of 10 repetitions each, separated by 1 min. Finally, breathing reeducation exercises, according to the Papworth method, will be implemented for 10 min, consisting of: (i) recognition of the abnormal breathing pattern, and practicing stomach and nose breathing retraining, (ii) slow breathing and controlled breath holding, (iii) relaxation techniques training, (iv) progressing breathing retraining in everyday life, with emphasis on postural correction, and (v) breathing reeducation exercises for home use, with the help of a booklet and videos, with emphasis on postural correction and with the instruction to practice these at least once per day. 

**Group B:** This group will receive CMT/soft tissue therapeutic techniques, plus sham DMT. Initially, the same manual therapy for the cervical spine (according to the Mulligan Concept and soft tissue techniques) as that used in Experimental Group A will be administered for 20 min. Additionally, sham DMT will be applied via therapeutic ultrasound (Sonopuls 692 Enraf-Nonius) sham administration in the sitting position for 10 min [38]. The equipment will be switched on, but the intensity will not be raised (0 W/cm^2^); therefore, the equipment will appear working, but no therapeutic dosage will be administered. The same therapist will carry out all the sham ultrasound techniques. Moreover, for 10 min, guidelines for activities of daily living (housekeeping: cleaning, sweeping) will also be provided, with emphasis on postural correction.

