**Group C:** This group will receive a typical conventional physiotherapy program, therefore acting as an active control group for this trial. Initially, Transcutaneous Electric Nerve Stimulation (TENS) will be applied, with a pulse duration of 250 microseconds at a frequency of 80 Hz for 15 min in the suboccipital region and the trapezius bilaterally. Then, Pulsed Microwave Diathermy (Enraf-Nonius RADARMED 950+), will be applied in the sitting position, for 10 min. Soft tissue techniques (deep soft tissue massage) will be applied at a slow speed for 15 min. Massage therapy, included gliding and kneading techniques will be applied over the trapezius (upper, lower, and middle fibers), splenius capitis, and levator scapulae muscles [53].

At the end of the interventions, leaflets will be given to the participants of Group B and Group C, describing general stretching exercises for the cervical spine.

Further details of the techniques applied are provided in the Supplementary Materials. However, leaflets with intervention details will be provided to participants of all groups to enhance adherence to the program, as the exercises will also be performed by participants at home. 

At the end of the trial, subjects will be asked which group they thought they were allocated in, to determine any potential bias.

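### Participants are called blinded, but the three programmes are visibly different, NDI and VAS are self-reported, and technique is aliased with therapist in A-C and partly aliased in A-B and B-C

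*Protocol article*

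**What the plan says.** Section 2.1 of the protocol article states the design: "This protocol describes a randomized clinical trial (RCT) with a blinded assessor and participants". The primary outcomes are the Neck Disability Index and pain on a visual analogue scale (2.9). Section 2.9.1 describes the first thus: "The NDI is a disability self-report tool in relation to neck pain". It describes the second as: "Subjective pain intensity registration, by the selection of a value between 0 (no pain) and 100 (maximal pain").

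Section 2.12 assigns the manual therapy to the main researcher. A second physiotherapist "will administer the traditional physiotherapy program (Group C) and the sham diaphragmatic manual therapy component (Group B"). On B's comparator it says: "sham DMT will be applied via therapeutic ultrasound", with the device switched on at zero intensity. It also says that "leaflets with intervention details will be provided to participants of all groups". The only blinding check is in the same section: "At the end of the trial, subjects will be asked which group they thought they were allocated in".

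Section 2.4 has patients receive detailed written information on objectives and methods before consent. Section 2.15 plans the contrasts A-B, A-C and B-C. In the Discussion, the limitations admit only an unblinded treating physiotherapist, and the active control is justified partly by blinding. The Conclusions list examiner blinding alone among the reasons to expect high internal validity.

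**The concern.** When the participant is the rater, keeping the examiner unaware of allocation does nothing for the rating. If participants can tell which programme they are in and expect more from one than another, that expectation can enter NDI and VAS directly. A reader who takes section 2.1 at face value would discount this source of bias.

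A second issue concerns what a difference can be attributed to. Where one arm is treated by one person and the comparator by another, technique and therapist cannot be separated by any analysis of the trial data, and recruiting more patients does not help. The main researcher also owns the practice, approaches patients for recruitment (2.6), answers their questions (2.4) and delivers the manual therapy. An effect of this person on patients' expectations is therefore plausible, although the article gives nothing to size it.

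**Working it through.** The article gives no figure on this point to reproduce. The check compares its own statements, counts therapist minutes, and adds two illustrations whose inputs are assumptions.

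**1. What each participant experiences (2.12)**

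| Minutes | A | B | C |
|---|---|---|---|
| Neck or main part | 20, neck mobilisation and soft tissue | 20, same as A | 15 TENS, 10 diathermy, 15 massage |
| Diaphragm part | 10, hands-on techniques | 10, zero-output ultrasound | none |
| Last part | 10, breathing training, plus home practice with booklet and videos | 10, daily-living and posture advice | none |
| Total | 40 | 40 | 40 |

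An ultrasound head does not imitate a hands-on technique, and nothing in B or C imitates breathing training. With the written information on methods (2.4) and the leaflets (2.12), a participant can recognise the programme received.

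**2. Who is blinded, place by place**

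- 2.1: assessor and participants.
- Discussion, limitations: the treating physiotherapist is not blinded; participants are not mentioned as a limitation.
- Conclusions: examiners only.

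The three places do not make the same claim, and only the first covers the people who rate NDI and VAS.

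**3. Therapist minutes per 40-minute session**

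The main researcher gives the manual work: 20 + 10 = 30 min in A and 20 min in B. The second therapist gives all 40 min of C and the 10 min of sham in B. The article does not name who gives the last 10 min in A or in B.

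- A-C: 30 of 40 min differ by therapist as documented, and 40 of 40 on the natural reading that the main researcher also gives A's breathing training.
- A-B: 10 of 40 (25%) if the same person gives the last 10 min in both arms. If the second therapist gives B's advice and the main researcher gives A's training, 20 of 40 (50%).
- B-C: 20 of 40 (50%), or 30 of 40 (75%) if the main researcher gives B's advice.

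**4. Illustration of aliasing in A-C (the therapist ICC is assumed; the article gives none)**

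The two therapists are treated as draws from a population of therapists, with n = 30 per arm (2.14). Design effect DE = 1 + (n - 1) x ICC. The true type I error for technique is 2 x [1 - Phi(1.96 / sqrt(DE))].

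| ICC | DE | Type I error |
|---|---|---|
| 0 | 1.00 | 0.050 |
| 0.01 | 1 + 29 x 0.01 = 1.29 | 0.084 |
| 0.02 | 1.58 | 0.119 |
| 0.05 | 2.45 | 0.211 |
| 0.10 | 3.90 | 0.321 |

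At 300 per arm and ICC 0.05, DE = 1 + 299 x 0.05 = 15.95 and the error is 0.62, so sample size does not repair it.

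**5. Illustration of an expectation shift (size assumed)**

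For a pure shift of d SD in one two-arm comparison of means, the chance of significance is about Phi(d x sqrt(n/2) - 1.96).

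- d = 0.3: 0.3 x sqrt(15) = 1.16, giving about 21%.
- d = 0.5: 0.5 x sqrt(15) = 1.94, giving about 49%.

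This simplifies the planned group-by-time analysis and shows only the order of magnitude.

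**6. The guess question**

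It is asked once, at the end of the trial. A high rate of correct guesses would show that participants know their group. It would not show whether they knew from the outset or inferred it from improvement, and it does not bear on therapist effects.

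**The case against.** The strongest reply is that the protocol does not set out to isolate a technique. Its first aim concerns the three components in combination, and the Discussion says that the specific components are not yet determined. A randomised comparison of whole packages, therapist included, remains valid. That stands, and it limits the point to attribution and to the blinding label.

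It can also be said that participants may know what they receive without knowing which arm is experimental or that the ultrasound delivers nothing. Sessions are individual and every arm gets a plausible treatment. The participant information is not shown, and nothing says that a leaflet describes the other arms. This also stands. A reader might infer that no blinding of any kind exists; the documents do not go that far. They do show that the unqualified label lacks support.

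Other stronger readings are not supported either:

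- That B-C is fully confounded by therapist. B is treated by both therapists.
- That the end-of-trial guess is useless. It can reveal awareness of group.
- That the bias is known to favour A. The therapists have 20 and 17 years of experience, and the main researcher also gives B's neck treatment.
- That all outcomes are exposed alike. The second aim concerns respiratory outcomes, several of which (end-tidal CO2, respiratory rate, chest expansion) are measured by instrument or tape. The self-report argument does not carry over to these, although the therapist aliasing does.

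**Conclusion.** The concern holds in this limited form. The statement that participants are blinded is not supported by the interventions described and is not repeated in the Conclusions. For NDI and VAS, protection is at most partial, through possible unawareness of the hypothesis or of the sham's inactivity. Therapist and technique are aliased in A-C, on the reading that the main researcher also gives A's breathing training; 30 of 40 minutes are certain. They are partly aliased in A-B (10 to 20 of 40 minutes) and B-C (20 to 30 of 40).

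The size of any bias is unknown. The type I error and expectation figures rest on assumed ICCs and shifts, and the former applies only if the question is about technique and not about these two therapists' packages. A-B is the least confounded contrast, but it tests the added diaphragm-plus-breathing package against ultrasound and advice, not a single technique. Randomised package comparisons survive. The label and the attribution need correcting.

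**What to change.** 1. In section 2.1, describe the trial as assessor-blinded, with participants at most unaware of the hypothesis and of the sham's status. Add participant awareness and therapist aliasing to the limitations in the Discussion. Cost: wording.
2. Collect a short expectancy rating and the group guess after the first or second session, and keep the guess at the end. Cost: one brief form. An early expectancy rating cannot be obtained in retrospect, and section 2.13 says that the trial has not started.
3. Where scheduling allows, let the same existing therapist deliver the whole of A and B, and state who gives the last 10 minutes in each. Moving the sham takes 10 min x 10 sessions x 30 patients = 3000 min = 50 h. If the second therapist was to give B's advice, moving that adds another 50 h. The downsides are more load on one therapist, who stays unblinded and whose capacity the article does not give, and a B-C contrast that then becomes fully aliased with therapist.
4. Report all contrasts as package comparisons: A-C and B-C as package-plus-therapist, and A-B as the least confounded contrast for the added diaphragm-plus-breathing package. Cost: wording.

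Section 2.2 requires important modifications to go to the ethics committee; items 2 and 3 would probably count.

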### 2.4. Recruitment Procedures

The patients will be recruited from primary care orthopedic practices located near the physiotherapy practice associated with the University of West Attica for this trial, using information leaflets and posters provided at the collaborating orthopedic practices and referrals from orthopedic or spinal surgeons.

Participants will be patients with diagnosed NSCNP of a mechanical nature, referred by orthopedic or spinal surgeons for physiotherapy, provided by their public insurance, concerning their neck pain condition. Patients will contact the physiotherapy practice to book an initial appointment, where they will be informed in detail about the objectives, methods, and details of the study via relevant written material. Clarifications will be provided by the main investigator, should any questions arise. Then, if patients agree to take part, they will be provided with a consent form to read and sign.

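### Section 2.1 calls the participants blinded, but the arms differ visibly and the sham does not imitate the hands-on technique, so the self-rated primary outcomes can include expectation

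*Protocol article*

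**What the plan says.** Section 2.1 makes an unqualified statement about blinding: "This protocol describes a randomized clinical trial (RCT) with a blinded assessor and participants". Other sections bear on it.

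- **Information to patients (2.4).** Before consent, "they will be informed in detail about the objectives, methods, and details of the study via relevant written material".
- **Group A (2.12).** Cervical manual therapy for 20 minutes, hands-on diaphragm techniques for 10, and breathing exercises for 10. The exercises begin with "recognition of the abnormal breathing pattern, and practicing stomach and nose breathing retraining" and extend to "breathing reeducation exercises for home use, with the help of a booklet and videos".
- **Group B (2.12).** The same 20 minutes of cervical manual therapy. Then "sham DMT will be applied via therapeutic ultrasound (Sonopuls 692 Enraf-Nonius) sham administration in the sitting position for 10 min", with the device on and the output at 0 W/cm². The last 10 minutes are advice on daily activities.
- **Group C (2.12).** TENS, pulsed microwave diathermy and massage.
- **Leaflets (2.12).** To support adherence, "leaflets with intervention details will be provided to participants of all groups".
- **Check on blinding (end of 2.12).** Patients are asked at the end of the trial to guess their group.
- **Primary outcomes (2.9 and 2.9.1).** NDI and pain VAS, both rated by the patient.
- **Discussion and Conclusions.** The limitations name only the treating physiotherapist as unblinded and give blinding as one reason for the active control. The Conclusions list blinding of examiners as a strength and do not list participants.

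**The concern.** Section 2.1 presents participant blinding as a property of the trial, yet patients can see and feel what distinguishes the arms. The component called sham diaphragmatic therapy is a machine applied to a seated patient. It can hide that the ultrasound is inactive, but it does not resemble a manual diaphragm technique. No arm receives an imitation of the breathing training.

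This matters because of who rates the outcomes. Assessor blinding protects measures that an assessor takes or judges. It does little for NDI and VAS, or for the secondary NQ, HADS and TSK, where the patient supplies the score. For these outcomes participant blinding is the relevant safeguard, and it is the one that is claimed but not delivered. A reader who relies on section 2.1 would attribute the whole of an A-C or A-B difference to the treatment components, although part of it could be expectation.

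**Working it through.** **1. What a patient can observe, arm by arm (section 2.12)**

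| Feature | A | B | C |
|---|---|---|---|
| Cervical manual therapy, 20 min | yes | yes | no |
| Diaphragm component, 10 min | hands-on | ultrasound device at 0 W/cm² | none |
| Breathing training, 10 min | yes | none (advice on daily activities) | none |
| Electrotherapy | none | inactive ultrasound | TENS 15 min, diathermy 10 min |
| Massage, 15 min | no (soft tissue work within the cervical therapy) | no (as A) | yes |
| Home material | breathing booklet and videos | stretching leaflet | stretching leaflet |
| Therapist | main researcher | main researcher, plus second therapist for the sham | second therapist |

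Session length is the same in all arms: 20 + 10 + 10 = 40 minutes in A and in B, and 15 + 10 + 15 = 40 minutes in C. Contact time is therefore matched, but content is not. A and C share almost nothing. A and B share half of each session (20 of 40 minutes) and differ openly in the other half.

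**2. What a patient is told**

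Section 2.4 says objectives and methods are explained in writing. The first objective in section 1 names cervical and diaphragm manual therapy combined with breathing re-education. The patient material itself is not shown. It is therefore not known whether it describes the other arms, labels one as experimental, or says which is expected to do better.

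**3. Whether a safeguard closes the gap**

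- The active control gives every patient some treatment. That may reduce disappointment, but it does not conceal which treatment is given.
- The allocation guess is asked once, at the end, when a patient's own improvement can colour the answer. It measures unblinding afterwards.
- The limitations do not mention participants.

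**4. Illustration of size**

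The documents give no figure for expectation bias, so there is nothing to reproduce. Inputs: n = 30 per arm (section 2.14); 5% significance level (section 2.15), taken as two-sided; true effect zero; patient ratings in A shifted by an assumed δ in SD units.

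*A single pairwise test without an omnibus test first.* The standard error is √(2/30) = 0.258 SD. The normal approximation to the rejection rate is Φ(δ/0.258 − 1.96) + Φ(−δ/0.258 − 1.96).

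- δ = 0.2: 0.121
- δ = 0.3: 0.213

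With 27 per arm (30 × 0.9), the rates are 0.114 and 0.197.

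*Closer to the plan.* Section 2.15 runs post hoc tests only if the interaction is significant. A simplified simulation at one time point, with only A shifted, applied a three-group F test first and then unadjusted pairwise tests:

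| δ (assumed) | A-B declared different | A-B or A-C declared different |
|---|---|---|
| 0 | 2.5% | 4% |
| 0.2 | 7% | 11% |
| 0.3 | 14% | 20% |

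The omnibus step holds the A-B rate below 5% when there is no bias, so the rise should be read from 2.5% as well as against the nominal 5%. The simulation ignores the repeated measures, the baseline and the second primary outcome.

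**The case against.** The best defence is that patients can know what they receive and still be blind in the sense that matters most, namely which programme is favoured. Section 2.4 does not say that patients learn the content of the other arms or the expected ranking. The leaflets are for adherence and may describe only the patient's own programme, and all arms take material home. Session number and length are equal, A and B share the cervical therapy, and the inactive ultrasound looks as if it is working. The authors plan an allocation guess, so they treat blinding as something to test, and the Conclusions claim only examiner blinding. Full participant blinding is hardly attainable for manual therapy and breathing training.

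Most of this stands, and it limits what may be concluded. A reader might infer that patients will know they are in the favoured or unfavoured arm. The documents do not support that, because the patient material is not shown. A reader might also infer that results will be reported as coming from a participant-blinded trial; the Conclusions point the other way. The lack of a sham in Group C is not a defect, since it is openly an active control.

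The defence does not rescue the sentence in section 2.1. The article describes no masking of the hypothesis, and if that is what is meant, section 2.1 should say so. That blinding is infeasible is a reason not to claim it.

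**Conclusion.** The claim of blinded participants in section 2.1 is wrong as written. The interventions in section 2.12 differ visibly, the sham does not imitate the hands-on technique, and nothing imitates the breathing training. Patients may be unaware of which programme is favoured, but the article does not say so.

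NDI and VAS are self-rated, so A-C differences can include expectation. A-B differences can too, to a lesser extent because those arms share the cervical therapy. The size is unknown. The 7% to 14% for A-B rests on an assumed shift of 0.2 to 0.3 SD in favour of A, 30 per arm, and a simplified one-time-point version of the planned sequence. The 12% and 21% from a single pairwise test without the omnibus step are tempting to cite, but they do not describe the plan, which tests the interaction first. None of this shows that the bias exists or that the A-B contrast is uninformative. It shows that the stated safeguard is not in place for the primary outcomes.

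**What to change.** 1. In section 2.1, describe the trial as assessor-blinded, with participants not blinded to the treatment received. If patients are not told which programme is favoured, say that and no more.
2. In the limitations, add that NDI, VAS, NQ, HADS and TSK are rated by patients who are aware of their treatment.
3. Describe Group B's component as inactive ultrasound that does not imitate the diaphragm technique, and do not interpret A-B as a fully sham-controlled contrast.
4. Word the information sheet and leaflets neutrally, as three physiotherapy programmes, without labelling any as experimental or sham or saying which is expected to do better. If they already read this way, state it.
5. Report the planned allocation guess by arm alongside the primary results.
6. If an expectancy rating is added, collect it before treatment starts or report it descriptively only. A rating taken after the first session can itself be affected by treatment, so adjusting for it would condition on a post-randomisation variable and could remove real early benefit.

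Allocation, sample size, treatments and the primary analysis are unchanged. The cost is a less favourable blinding claim and a small ethics notification for any change to patient material. The article says the trial had not started, so the materials could still be changed at that point.
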